## 13.2. Key and secondary endpoint analysis

For the following key endpoints, the familywise type I error rate (FWER) will be controlled at two sided  $\alpha = 0.05$ . A gatekeeping strategy will be used, where the primary endpoint will be tested first, if passing the significance testing, other key endpoints will be tested in the order listed below using the fixed-sequence method at  $\alpha = 0.05$ .

### Key endpoints

- Proportion of time spent in the target glucose range (3.9 to 10.0mmol/l)
- Mean sensor glucose
- Proportion of time spent above target glucose ( $>10.0\text{mmol/l}$ )
- Non-inferiority for time spent below target glucose ( $<3.9\text{mmol/L}$ )

The following endpoints will be considered exploratory and Benjamini-Hochberg false discovery rate (FDR) adjusted p-values will be calculated within each subcategory below:

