### **3.4.2. Closed-loop studies in adults with type 2 diabetes in the inpatient setting**

The Cambridge fully closed-loop system has been shown to be safe and feasible in insulin naïve patients with type 2 diabetes (T2D) in a clinical research facility setting (38). We have previously assessed fully closed-loop insulin delivery in non-critical care patients with T2D hospitalised in the general wards (28, 39). In a multi-national study, 136 adults with T2D who required insulin therapy

were randomised to receive either closed-loop insulin delivery or conventional subcutaneous insulin therapy for up to 15 days or until hospital discharge (28). The mean percentage of time that the sensor glucose measurement was in the target range was 65.8% in the closed-loop group and 41.5% in the control group, a difference of 24.3 percentage points ( $P<0.001$ ); values above the target range were found in 23.6% and 49.5% of the patients, respectively, a difference of 25.9 percentage points ( $P<0.001$ ). The mean glucose level was 8.5 mmol/l in the closed-loop group and 10.4 mmol/l in the control group ( $P<0.001$ ). There was no significant between-group difference in the duration of hypoglycaemia or in the amount of insulin that was delivered. Among inpatients with T2D receiving noncritical care, the use of a fully automated, closed-loop insulin-delivery system resulted in significantly better glycaemic control than conventional subcutaneous insulin therapy, without a higher risk of hypoglycaemia.

We have also assessed fully automated closed-loop insulin delivery in non-critical care patients requiring insulin therapy who were receiving enteral or parenteral nutritional support. Forty-three adults were randomised to receive either closed-loop insulin delivery or conventional subcutaneous insulin therapy for up to 15 days or until hospital discharge (29). Results showed that closed-loop increased time spent within target glucose range (3.9-10.0mmol/l) from 36.4% to 68.4%, a difference of 32 percentage points ( $p<0.001$ ). This showed that fully-closed loop insulin delivery is an effective treatment option to improve glycaemic control in inpatients receiving nutritional support.

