## **7.5. Precautions**

During treatment with insulin there is a risk of hypoglycaemia and hyperglycaemia. In-hospital testing and hazard analysis have documented reduced risk of hypoglycaemia and hyperglycaemia during closed-loop compared to conventional treatment.

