#### 9.1.2. Other key endpoints

- Proportion of time spent in the target glucose range (3.9 to 10.0mmol/l)\*
- Mean sensor glucose\*
- Proportion of time spent above target glucose (>10.0mmol/l) \*
- Non-inferiority for time spent below target glucose (<3.9mmol/L) \*

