### **10.4. Benefits**

It is expected that the fully closed loop system may have an important role in the management of diabetes in people with type 2 diabetes.

The closed-loop system may impact on the frequency of hypoglycaemia with suspected fewer low glucose levels with closed-loop insulin delivery compared with usual care. In addition to this, higher blood glucose levels above target should be reduced with use of the closed-loop algorithm. In the closed-loop arm, participants will not need to self-administer insulin injections, which may facilitate diabetes management. In the control arm, participants will not need to monitor glucose levels with

finger-stick glucose checks, which may facilitate diabetes management. Therefore, participation in this study is likely to be beneficial for study participants.

It is possible that participants will not directly benefit from being a part of this study. However, during the run-in and training, the participant will have close contact with the study team and / or diabetes educator. The CGM data provided during the study may also help participants to optimise their usual insulin therapy and diabetes self-management.

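### The confirmatory sequence in 13.2 stops at non-inferiority for time below 3.9 mmol/l; a final superiority step would cost no alpha, patients or data (low severity)

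*Protocol*

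**What the plan says.** Section 13.2 sets up the confirmatory family. For the key endpoints, "the familywise type I error rate (FWER) will be controlled at two sided" 0.05. HbA1c is the gatekeeper, and if it passes, "other key endpoints will be tested in the order listed below using the fixed-sequence method". The order is time in range, mean sensor glucose, time above 10.0 mmol/l, and finally "Non-inferiority for time spent below target glucose". The synopsis and section 9.1.2 ("Non-inferiority for time spent below target glucose (<3.9mmol/L") state the hypothesis for this endpoint in the same way.

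Section 13.2 then classes everything after the key list as exploratory, with Benjamini-Hochberg adjusted p-values within subcategories. The low-glucose measures there are time below 3.5 and below 3.0 mmol/l. Time below 3.9 mmol/l does not reappear.

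On what is anticipated, section 10.4 says that closed-loop may affect the frequency of hypoglycaemia, with "suspected fewer low glucose levels with closed-loop insulin delivery compared with usual care". Section 3.4.3 reports less time below 3.9 mmol/l with closed-loop in adults with type 2 diabetes on dialysis (p=0.040), and no increase in the 8-week crossover study. For the multinational inpatient trial, section 3.4.2 reports: "There was no significant between-group difference in the duration of hypoglycaemia".

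**The concern.** A fixed sequence gives confirmatory status only to the hypotheses it names. For time below 3.9 mmol/l it names one: that closed-loop is not worse by more than a margin. If the data showed a clear reduction, that result would have no place in the error-controlled family. It would have to be reported as an unadjusted or post hoc observation beside a confirmed statement of non-inferiority.

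This matters somewhat more here because time below 3.9 mmol/l is the only hypoglycaemia measure in the confirmatory family. Under 10.1.2 and 10.2.3, non-severe hypoglycaemia is not recorded as an adverse event, and 13.3 compares severe events only if there are enough of them. Sensor time below range is therefore the main quantitative evidence on ordinary lows. Section 3.2 makes the avoidance of hypoglycaemia a central consideration when insulin is intensified. A confirmed reduction alongside lower HbA1c would be a stronger conclusion than the plan now allows, from data already being collected.

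**Working it through.** **1. Where the endpoint appears.** Synopsis, 9.1.2 and 13.2 (key endpoints): non-inferiority only, last in order. 9.1.3 and 13.2 (secondary): below 3.5 and below 3.0 mmol/l only. 9.1.4 (exploratory): day/night control and monthly trends, with no low-glucose hypothesis named. Superiority for below 3.9 mmol/l is in none of these lists.

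**2. The protocol's own sample size (13.11).** Inputs: difference 0.8, SD 1.2, two-sided 0.05, power 90%.

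n per arm = 2 × (1.960 + 1.2816)² × (1.2/0.8)² = 2 × 10.51 × 2.25 = 47.3, rounded up to 48, so 96 in total. This reproduces the stated figure (power at 48 per arm is 0.904). Allowing for 20% dropout gives 96/0.8 = 120; the protocol attributes the rest of the rise to 224 to greater exposure for safety and feasibility.

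**3. Why a last step costs no alpha.** Let d be the true difference in time below 3.9 mmol/l (closed-loop minus control) and M > 0 the margin. The non-inferiority null is d ≥ M; the one-sided superiority null is d ≥ 0, which contains it. The new step is opened only after all five existing tests have passed, and each test is made at full alpha only if its predecessors passed. No earlier test loses alpha or power. In practice the same 95% confidence interval is read first against M and then against zero.

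**4. Simulation check.** 2,000,000 runs per scenario, correlations of 0, 0.5 and 0.8 between endpoints, superiority counted only in the favourable direction. M was set at 3 standard errors because the protocol gives no margin.

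| True state | Familywise error without the step | With the step |
|---|---|---|
| No effect on any endpoint | 0.050 | 0.050 |
| Only HbA1c improved | 0.050 | 0.050 |
| First four endpoints improved, d = 0 | 0.000 | 0.025 |
| First four improved, d = M | 0.025 | 0.025 |

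The third row is the only one that moves, and it stays below the 0.05 allowed. Setting M at 1.5 standard errors gives the same 0.025. If the true reduction is 3 standard errors and the first four endpoints are effective, non-inferiority passes in over 99.9% of runs and superiority in 85%. Under the present wording those 85% could not be claimed in the confirmatory family.

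**5. What the step could detect.** Evaluable participants: 224 × 0.8 = 179.2, about 89.5 per arm. The protocol gives no SD for this endpoint, so SDs of 1.0, 1.5 and 2.0 percentage points are assumptions.

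Standard error = SD × √(2/89.5) = SD × 0.1495. Detectable difference at 80% power = (1.960 + 0.8416) × standard error = 0.419 × SD.

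- SD 1.0: 0.42 points
- SD 1.5: 0.63 points
- SD 2.0: 0.84 points

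Power of the superiority test taken alone, by standardised difference:

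| Standardised difference | 112 per arm | 90 per arm |
|---|---|---|
| 0.2 | 0.32 | 0.27 |
| 0.3 | 0.61 | 0.52 |
| 0.4 | 0.85 | 0.77 |
| 0.5 | 0.96 | 0.92 |

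These are normal approximations on the untransformed scale; 13.2 provides for transformation of highly skewed secondary endpoints.

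**The case against.** The strongest reply is that nothing here is wrong. No objective in section 4 claims less hypoglycaemia; 4.2 is to evaluate safety. The rationale in 3.5 is better control without added hypoglycaemia, and the inpatient trial and the 8-week crossover study in 3.4 both reported no increase. Non-inferiority is the hypothesis that matches that case. This stands, and it is why the point is a low-severity improvement.

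A second reply is that 13.1 announces a separate analysis plan, which could add the step, and that lows are compared between arms elsewhere: below 3.5 and below 3.0 mmol/l in 13.2, and severe hypoglycaemia in 13.3 if events suffice. Both are true. However, the first two are labelled exploratory, the third is a conditional safety comparison outside the sequence, and the protocol itself fixes the ordered list. The step therefore belongs in 13.2 as well as in the analysis plan.

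Third, the gain is uncertain. The step is reached only if all five earlier tests succeed, no SD or control-arm level is given, and a reduction cannot exceed the control arm's own mean time below range. If lows are already rare in the control group, there is little room to show fewer. This limits the likely benefit but not the argument about cost.

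Three stronger readings are tempting and not supported:

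- That fewer lows is a study hypothesis left untested. Section 10.4 is a benefits paragraph in hedged terms and states no hypothesis.
- That a reduction is permanently shut out. The limit applies to the protocol's hierarchy as written; the analysis plan was not at hand and may extend it, and an estimate can be reported either way.
- That 7.5 must be rewritten because it says "In-hospital testing and hazard analysis have documented reduced risk of hypoglycaemia and hyperglycaemia during closed-loop compared to conventional treatment" while 3.4.2 found no significant difference in duration. Section 7.5 is background on in-hospital testing and hazard analysis, and concerns risk, whereas 3.4.2 gives the duration of hypoglycaemia in one trial. A superiority test in this home study could not verify it.

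**Conclusion.** The point holds as a free improvement of low severity. As the protocol stands, a reduction in time below 3.9 mmol/l has no place in the confirmatory family beyond non-inferiority. A final superiority step would give it one while leaving the sample size at 224 and the five existing tests untouched.

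The error-control conclusion rests on the fixed-sequence structure and the nesting of the two nulls. It needs no assumption about the SD or the value of the margin. The detectable differences rest on assumed SDs, 20% loss and a normal approximation, and show only the order of magnitude; whether such reductions are attainable cannot be judged from the protocol.

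**What to change.** Keep non-inferiority as it is. Add one sentence after the last key endpoint in 13.2, repeat the step in 9.1.2 and the synopsis, and carry it into the analysis plan:

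*If non-inferiority for time <3.9 mmol/l is shown, superiority will be tested next at two-sided alpha 0.05.*

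A reduction would be claimed only if the whole confidence interval favours closed-loop. The change should be made before any between-group results are seen. It costs a short amendment and needs no additional participants, data or alpha. Section 7.5 needs no change for this point.

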### Secondary endpoints

#### *Glucose related indices:*

- Standard deviation and coefficient of variation of glucose
- Proportion of time with glucose  $<3.5\text{mmol/l}$  and  $<3.0\text{mmol/l}$
- Proportion of time with glucose  $>13.9\text{ mmol/l}$ ,  $>16.7\text{mmol/l}$  and  $>20.0\text{mmol/l}$
- Binary metrics for HbA1c (HbA1c  $<7.0\%$ , HbA1c  $<7.5\%$ )

#### *Insulin and other endpoints:*

- Total daily insulin dose
- Body weight, waist hip ratio and Body Mass Index
- Blood pressure
- Fasted lipid profile
- Renal function as measured by sodium, potassium, urea, serum creatinine, estimated Glomerular Filtration Rate and urinary albumin creatinine ratio
- Liver function as measured by liver markers (ALT, AST, ALP,  $\gamma\text{GT}$ , bilirubin and albumin) and FIB4 index

Trends in CGM and insulin data collected within intervention arms will be evaluated on a monthly basis and daytime (0600 to 2359) and overnight (0000 to 0559) glucose control will be evaluated separately.

For the pre-specified key endpoints and secondary endpoints, mean  $\pm$  SD or summary statistics appropriate to the distribution will be reported for the primary endpoint over the 26 week period by treatment intervention and tabulated by treatment group. Analysis of secondary endpoints will parallel the primary analysis. A transformation will be applied to all highly skewed secondary endpoints.

### **13.3. Safety Evaluation**

Safety data including severe hypoglycaemia events will be tabulated for all participants, including drop-outs and withdrawals, irrespective of whether CGM data are available and irrespective of whether closed-loop was operational. All adverse events will be listed for the entire study duration.

For each of the following safety outcomes, mean  $\pm$  SD or summary statistics appropriate to the distribution will be tabulated by treatment group:

- Number of severe hypoglycaemia events
- Number of participants with any severe hypoglycaemia event
- Number of diabetic ketoacidosis events
- Number of participants with any diabetic ketoacidosis event
- Number of adverse events per participant
- Number of serious adverse events per participant

For severe hypoglycaemia (if enough events), the event rates will be compared using a repeated measures regression model.

### **13.4. Utility Evaluation**

The amount of CGM use will be tabulated for each treatment arm, in addition to the amount of closed-loop system use in the closed-loop arm. Summary statistics appropriate to the distribution and range will be reported.

### **13.5. Questionnaires**

Descriptive tabulations of questionnaires will be carried out, and scores will be calculated using provided scaling and scoring tools as appropriate.

### **13.6. Participant Interviews**

To maximize rigor, at least two experienced qualitative researchers will be involved in data analysis. A thematic analysis will be undertaken by these individuals who will independently review data and write separate reports before attending regular meetings to compare their interpretations and reach agreement on recurrent themes and findings. Interviews will be read through repeatedly and cross-compared in order to identify issues and themes which cut across different people's accounts. A key aspect of the analysis will focus on understanding the impact of using a closed loop on diabetes self-management practices and quality of life compared with their accounts of self-managing their diabetes using standard insulin therapy pre-trial. A final coding frame, reflecting the initial research questions and emergent themes, will be developed once all data have been reviewed and consensus reached on key themes and findings.

### **13.7. Healthcare Professional Interviews**

To maximise rigor, at least two experienced qualitative researchers will be involved in data analysis. These researchers will independently review interview transcripts (data immersion) and use the method of cross comparison to identify issues and themes that cut across healthcare professionals' accounts. A final coding frame, reflecting the initial research questions and emergent themes, will be developed once all data have been reviewed and consensus reached on key themes and findings.

### **13.8. Evaluative periods**

The primary and secondary measures will be calculated from day 1 until the end of the 26 week study intervention. Where appropriate, sensor-based measures will also be calculated for day and night-time periods. The interval from 0600 to 2359 defines day-time period, 0000 to 0559 defines the night-time period.

### **13.9. Interim monitoring and analysis**

No formal interim analysis will be performed. Interim analyses of the safety data primarily will be performed at regular intervals (at least annually) for review by the DSMB. The DSMB members will comply with DSMB charter. The DSMB will be asked to give advice on whether the accumulated data from the trial, together with results from other relevant trials, justifies continuing recruitment of further participants or further follow-up.

### **13.10. Adherence and retention**

Protocol adherence will be assessed in each treatment group. Tabulations of protocol deviations and unscheduled visits will be included in the analysis. A flow chart will also be used to assess visit completion rates post treatment initiation.

### **13.11. Sample size and power calculations**

Data from two completed studies (30, 40) were considered when preparing the power calculations for this study. A sample size of 96 participants (48 per group) was determined to have 90% power to detect a difference in mean HbA1c level between treatment groups, assuming a population difference of 0.8%, an effective SD of the 26 week values of 1.2, and a two-sided type 1 error rate of 0.05. This number was increased to 224 (112 per group) to account for dropouts (assuming a 20% dropout rate) and to increase the number of participants who will be exposed to the closed-loop system for an enhanced safety and feasibility assessment. Recruitment will target a minimum quota of 25% of participants using basal insulin and a minimum quota of 60% of participants using multiple daily insulin injections.

A treatment group difference of  $\geq 0.5\%$  represents a clinically meaningful change in the HbA1c distribution and is generally associated with at least a 50% greater proportion of participants experiencing improvement in HbA1c level by 10% or more, which was shown in the Diabetes Control and Complications Trial to be associated with a substantial risk reduction in diabetic microvascular complications. This is further supported by the results of the United Kingdom Prospective Diabetes Study, which showed that any improvement in HbA1c level is associated with a reduction in risk of diabetic complications.

### **13.12. Deviations from the statistical plan**

Any deviations from the original statistical plan will be recorded and agreed by the Coordinating Investigator and by the Principal Investigators.

## **14. Case Report Forms**

The Case Report Form (CRF) is the printed, optical, or electronic document designed to record all the protocol required information to be reported to the Coordinating Investigator for each study participant.

CRFs will be completed in accordance with ISO 14155:2020 GCP standard. Corrections to the CRF will be performed by striking through the incorrect entry and by writing the correct value next to the data that has been crossed out; each correction will be initialled and explained (if necessary) by the Investigator or the Investigator's authorised staff.

If any amendments to the protocol or other study documents are made, CRFs will be reviewed to determine if an amendment to these forms is also necessary.

## **15. Data Management**

Confidentiality of participant data shall be observed at all times during the study. Personal details for each participant taking part in the research study and linking them to a unique identification number will be held locally on a study screening log in the Investigator Site File at each of the investigation centres. These details will not be revealed at any other stage during the study, and all results will remain anonymous.

Case report forms (CRFs) will be used for recording anonymised study data. The study identification number will be used on the CRF. Names and addresses will not be used.

The study identification number will be used on the blood samples that are collected and stored throughout the study. Collected samples will be stored securely and locked away. Only researchers directly involved in the study will have access to the samples.

Electronic data will be stored on password-protected computers. All paper records will be kept in locked filing cabinets, in a secure office at each of the investigation centres. Only members of the research team and collaborating institutions will have password access to the anonymised electronic data. Only members of the research teams will have access to the filing cabinet. All data will be stored in line with the General Data Protection Regulation (GDPR) (EU) 2016/679 and the Data Protection Act (DPA) 2018 and will be archived securely according to the Sponsor's archiving policy. In case of withdrawal of participants, anonymised data that were obtained before withdrawal will be used.

Direct access to the source data will be provided for monitoring, audits, REC review and regulatory authority inspections during and after the study. The fully anonymised data may be shared with third parties (EU or non-EU based) for the purposes of advancing management and treatment of diabetes.

Appropriate procedures agreed by the Coordinating Investigator and Clinical Principal Investigators will be put in place for data review, database cleaning and issuing and resolving data queries.

## **15.1. Switzerland**

Study data will be collected, managed and stored using REDCap electronic data capture tools hosted at the Department of Anaesthesiology and Pain Medicine, Inselspital, Bern University Hospital. REDCap® (Research Electronic Data Capture) is a secure application designed to support data capture for research studies, providing 1) an intuitive interface for validated data entry; 2) audit trails for tracking data manipulation and export procedures; 3) automated export procedures for seamless data downloads to common statistical packages; and 4) procedures for importing data from external sources [<https://projectredcap.org/resources/citations/>].

The study team in Bern will use the identical eCRF on REDCap.

Data within REDCap® are stored in relational database engines like PostgreSQL or Microsoft SQL server. REDCap® provides web application security and can be configured for Secure Socket Layer (SSL) encrypted data transfer if needed.

